### Adverse events

Potential challenges anticipated in the study include participant dropout, seasonal variations in fruit and vegetable availability, and possible contamination between intervention and control communities. The study incorporates regular monitoring, community engagement, and logistical planning to mitigate these risks. Additionally, potential discomfort during haemoglobin testing has been noted, with mitigation through trained phlebotomists and standard operating procedures.

### Ancillary and post-trial care

Given the low-risk nature of this nutrition education intervention, no formal provisions for ancillary or post-trial clinical care are planned. However, participants who experience any adverse effects related to study procedures, such as discomfort from blood sample collection, will be referred to the nearest health facility for appropriate care at no cost to the participant. Contact information for the principal investigator and healthcare personnel will be provided to all participants. While no financial compensation is offered for participation, all necessary precautions will be taken to minimise risk, and ethical obligations to ensure participant safety will be upheld throughout the study.

### Withdrawal

Participants may choose to withdraw from the research at any time without having to explain his/ her decision. The participant may choose not to answer any question they find uncomfortable or private. There will be no consequence, loss of benefit or care to any participant who chooses to withdraw from the study. However, some of the information obtained from participants without identifiers, before they decide to withdraw, may be modified or not used in final analysis reports and publications.

### Concomitant care and permitted interventions

During the trial, participants in both the intervention and control groups will be permitted to continue receiving their regular healthcare services, which are available in their communities, including antenatal care, child health services, and general outpatient care. However, any external nutrition-specific programs or food aid interventions targeting fruits and vegetables that are introduced in the study communities during the trial period will be considered prohibited interventions, as they may confound the study outcomes. Participants will be regularly monitored, and any involvement in such programs will be documented. Additionally, no therapeutic supplements, fortified foods, or nutrition-focused interventions outside the scope of the study will be allowed. This approach ensures that the effects measured are attributable solely to the study’s intervention on post-harvest loss reduction and nutrition education.

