### Haemoglobin testing

Capillary blood samples will be collected in the early morning (approx. 30°C, 80% humidity) using Hemocue® safety lancets. Procedures will follow WHO (33, 43) and Hemocue Hb 501 operating guidelines. Hands will be warmed and cleaned with 70% isopropyl alcohol. The third drop of blood (after discarding the first two) will be used to fill a microcuvette (~10 μL) for haemoglobin assessment using the Hemocue Hb 501 device. Samples will be taken from both women and children. Cuvettes not properly filled or with air bubbles will be discarded. Machines will be cleaned daily and validated using Hemotrol Level 1, 2, and 3 controls (Eurotrol E. V., Netherlands) (37, 38).

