### Adherence strategies and monitoring procedures

To ensure effective implementation of the intervention, this study will employ multiple strategies to improve adherence and monitor compliance. These include regular follow-up through bi-weekly phone calls and monthly home visits, simplified educational materials in local languages, non-monetary incentives such as recognition certificates, and participant feedback mechanisms to enhance engagement. Monitoring adherence will involve tracking attendance at educational sessions, conducting home visit assessments of storage practices, collecting monthly self-reports, and performing periodic dietary and anthropometric evaluations. These combined strategies aim to foster consistent participation, reinforce learning, and ensure reliable measurement of the intervention’s impact on nutritional outcomes.

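### The concomitant-care rule disallows therapeutic supplements and fortified foods with no exception for treatment given in the routine care it permits

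*Protocol article*

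**What the plan says.** The section Concomitant care and permitted interventions makes three statements in sequence.

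1. Both arms may go on using the health services in their communities, "including antenatal care, child health services, and general outpatient care".
2. External nutrition programmes or food aid aimed at fruits and vegetables that arrive during the trial are prohibited, and "any involvement in such programs will be documented".
3. As a further rule, "no therapeutic supplements, fortified foods, or nutrition-focused interventions outside the scope of the study will be allowed".

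The reason given is attribution. The section says that the approach "ensures that the effects measured are attributable solely" to the study's own intervention. No reason of safety or clinical need appears.

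The intervention consists of education and counselling (Intervention design and strategy), so the study itself supplies no therapeutic product.

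**The concern.** The first and third statements collide wherever permitted care includes a supplement or a therapeutic food. A child seen at a child health service may be treated under the first statement, while the third says the product is not allowed. The paragraph does not say which prevails.

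Safety is at stake. Anaemia status and anthropometry are primary outcomes (Table 2), so the trial can itself bring to light the conditions for which such treatment would be indicated. Staff who take the rule at its word could discourage or stop that treatment. There is also a reporting problem: if some staff applied the rule literally and others did not, a reader of the results could not tell what care participants received.

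**Working it through.** No sample size, power or error-rate figure is involved. The check is whether any other section supplies the missing exception.

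**Position of the rule.** The sentence on supplements and fortified foods opens with an additive word, so it goes beyond the preceding ban on external programmes. The phrase about the scope of the study may qualify all three listed items or only the last. On either reading, a supplement prescribed at an outpatient visit is not part of an education programme and falls within the words.

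**Other sections that might limit it.**

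- *Ancillary and post-trial care.* No formal ancillary care is planned. The one referral route is for "participants who experience any adverse effects related to study procedures". The commitment that "ethical obligations to ensure participant safety will be upheld throughout the study" makes the literal reading less likely, but it is general and does not lift the rule.
- *Inclusion and exclusion criteria.* Severe malnutrition is an exclusion only when complications need inpatient care, and anaemia is not named. The list of diseases is open-ended, so some children needing treatment may already be excluded. Uncomplicated severe malnutrition and anaemia are not clearly excluded.
- *Study setting.* Nutritional treatments and services in each group are to be recorded. This suggests that some treatment is expected, but it does not settle the matter, because the concomitant-care section both prohibits external programmes and documents involvement in them.
- *Withdrawal; Consent and participation; Ethics and dissemination.* Participants may leave without loss of care, and the trial adheres to the Declaration of Helsinki. Neither is an exception for someone who stays in the trial.

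**What the trial will see.** Under Haemoglobin testing, "Samples will be taken from both women and children", with no action stated for a low result. Z-scores are calculated for children (Anthropometric measurements). Adherence monitoring includes "performing periodic dietary and anthropometric evaluations", so growth is also looked at between baseline and the final assessment.

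**Time left when the text was fixed.** Inputs: start 1 August 2024 and planned end 31 July 2025 (Study status and timeline); Version 1.0 finalised 9 June 2025 (Protocol version and date).

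- Start to planned end: 364 days.
- Start to version date: 312 days.
- Remaining: 364 − 312 = 52 days; 52 / 364 = 14.3%.

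This is calendar time. Recruitment took up to a month, and the article does not say when the rule came into force.

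**The case against.** The strongest reply is that the paragraph should be read as a whole. It opens by permitting routine care, turns to outside inputs that could confound the outcomes, and gives attribution as the single purpose. On that reading, treatment within routine care stays allowed and only added inputs from elsewhere are barred. The record of nutritional treatments in both groups fits this. No section tells staff to stop treatment or describes enforcement, and the ethics board receives adverse-event reports. All of this stands as evidence of what was probably intended. It does not change what the sentence says, and the article nowhere states the narrower meaning.

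A second reply is that an article leaves operational detail to the full protocol. That holds for a rule on whom to refer after a low haemoglobin or z-score, and its absence here is not part of this point. It does not cover a prohibition that the article states without limit beside a conflicting permission.

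A third reply is that the correction comes late. Table 2 places haemoglobin testing only at baseline and after the intervention, so little of the period remained for a changed rule to act on. This stands, and it is why the fix includes reporting.

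A reader might also infer that continued routine care in both arms defeats the attribution claim. The documents do not support that. Care common to both arms is what a concurrent control group is there to handle; bias would need use that differs between arms, and nothing shows such a difference. The word solely is stronger than a prohibition can deliver, but it fixes no analysis.

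**Conclusion.** The point holds as a conflict in wording with a safety consequence, and it should be fixed. The paragraph permits routine care and then, without qualification, disallows therapeutic supplements and fortified foods. No other section of the article excepts clinical need.

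The rule covers all 140 women and their children. A reader might apply the anaemia rates under Study setting (48.9% of under-fives nationally, over 55% in regional hospital data) and conclude that about half the children were denied treatment. The documents do not support that: the rates concern any anaemia in other populations, and no section says that anyone was refused care. Neither a count of affected participants nor a size of bias can be given.

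The conclusion rests on two assumptions. Staff may act on the sentence as written, which is plausible because internal monitoring is meant to secure compliance with the protocol (Auditing of trial conduct). And routine services in these communities sometimes provide such products, which the article does not state. If the narrow meaning was intended and staff understood it so, no harm follows and the correction is one of clarity only.

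**What to change.** Limit the prohibition to external nutrition programmes or products introduced during the trial. Replace the sentence on supplements and fortified foods with text such as: Clinically indicated treatment, including supplements and therapeutic or fortified foods from routine care, is allowed in both arms and recorded in the same way in each. This extends the recording already promised under Study setting. Report use by arm with the results.

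Notify field staff and the ethics committee at once. If collection has ended, report how the rule was applied and whether any treatment was withheld because of it.

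The cost is a rewording of the paragraph, a notice to staff and the committee, and a summary of treatment use by arm. The downside is some possible dilution of the contrast for haemoglobin and anthropometry if participants receive outside treatment. That is a small price for removing a literal bar on indicated care.

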### Auditing of trial conduct

Formal external auditing of the trial is not planned due to the community-based nature and minimal risk profile of the intervention. However, internal monitoring will be conducted by the principal investigator and supervisory team to ensure compliance with the protocol, ethical standards, and data quality procedures. Periodic progress reports, including documentation of recruitment, adherence, and any adverse events, will be submitted to the ethics review board and the KNUST College of Science graduate school. While this monitoring is not independent of the investigators, it provides an appropriate oversight mechanism within the study’s operational context.

### Data monitoring

The nature of the trial may not need a data monitoring team, as the study supervisors will monitor the data collection and analysis processes. Periodic reports on the progress of the trial and adverse events will be submitted to the ethics review board by the researcher and supervisors.

### Data storage and management

All collected data will be anonymised using unique participant identification codes. Names and personally identifying information will not appear in any datasets. Data will be stored in password-protected computers with regularly updated antivirus software, accessible only to the research team. To ensure data integrity, the following quality assurance procedures such as double data entry for quantitative data using EpiData software to minimise errors, weekly consistency checks on a 10% random sample by the lead research assistant and monthly data audits by the principal investigator and a senior supervisor to verify protocol compliance and data completeness will be implemented. Focus group recordings will be transcribed, anonymised, and securely stored. Qualitative data will be stored separately from the code key. At study completion, anonymised datasets, analysis scripts, and the final protocol will be deposited in a secure institutional repository. Access will be granted upon a reasonable request and approval by the ethics board, if data protection and confidentiality guidelines are followed.

### Protocol version and date

This manuscript presents Protocol Version 1.0, finalised on June 9, 2025. Any future amendments to the protocol will be documented with a version number and date and reported to the ethics committee accordingly.

### Ethics and dissemination

The trial adheres to the ethical standards of the Declaration of Helsinki. Written informed consent will be obtained from all participants and/or their guardians before enrolment. Participation will be entirely voluntary, with no penalties for refusal or withdrawal. Ethical approval for the study was obtained from the Committee on Human Research, Publication, and Ethics (CHRPE) with reference number CHRPE/AP/044/25, and administrative clearance was secured from the Ho West District Assembly. The study is registered with the Pan African Clinical Trial Registry (PACTR202310582275172). Upon completion, anonymised datasets, statistical codes, and a full version of the protocol will be made publicly accessible through institutional repositories and shared upon reasonable request, ensuring transparency and compliance with ethical guidelines.

There are no restrictions on publication, and the research team is committed to transparent, timely, and responsible reporting in accordance with ethical guidelines and journal requirements. Authorship for any publications arising from this trial will follow the guidelines set by the chosen peer review journal. All individuals who make substantial contributions to the conception, design, data collection, analysis, interpretation, or manuscript drafting will be eligible for authorship and appropriately acknowledged. No professional medical writers will be employed for this study, and members of the research team will prepare all manuscripts to ensure transparency and intellectual ownership of the work.

### Public access to protocol, data and statistical code

The research team is committed to promoting transparency and reproducibility. Upon publication of the study findings, the full trial protocol, anonymised participant-level dataset, and statistical analysis code will be made available to the public upon reasonable request. These materials will be shared through institutional repositories or data-sharing platforms in accordance with data protection and ethical guidelines. Requests for access will be reviewed by the principal investigator and approved by the ethics committee to ensure compliance with confidentiality and responsible data use.

### Protocol amendments

Any significant modifications to the study protocol, such as changes to eligibility criteria, outcome measures, data collection procedures, or statistical analysis plans, will be formally documented and communicated to all relevant parties. These include the principal investigators, co-investigators, the ethics review committee (CHRPE), the Ho West District Assembly, and the Pan African Clinical Trial Registry. Updated versions of the protocol will include a new version number and date, and amendments will be reported in any resulting publications or trial reports in accordance with ethical and regulatory standards.

## Summary

The current study is grounded in the urgent need to address the dual challenges of post-harvest loss (PHL) and malnutrition, particularly in vulnerable populations such as women and children in rural Ghana. While PHL has been widely acknowledged for its economic challenges, its direct nutritional consequences remain inadequately explored in both scientific literature and policy discourse. This study was designed to respond to this gap by systematically examining how losses of nutrient-rich perishable foods, fruits and vegetables, along the value chain, compromise food availability, accessibility, and ultimately the nutritional status of women and children. This rationale is firmly rooted in the under-recognised link between food systems inefficiencies and public health outcomes.

The study offers three significant contributions. First, it aims to provide rigorous scientific evidence on the extent and drivers of PHL and their association with dietary diversity, food consumption scores, household hunger levels, haemoglobin concentrations, and anthropometric outcomes. Second, it introduces an integrated, community-based educational intervention aimed at improving knowledge and practices regarding post-harvest handling and consumption of fruits and vegetables. Third, the study contributes to policy development by generating context-specific, evidence-based recommendations for local and national decision-makers, agricultural stakeholders, and public health practitioners. These recommendations will support more resilient and nutrition-sensitive food systems.

The findings are expected to influence practice through the development of scalable educational models and post-harvest management strategies. On a policy level, results will provide an empirical basis for aligning agricultural and nutrition policies, especially in contexts where food loss directly undermines nutrition outcomes. The study also fills a crucial knowledge gap by demonstrating the direct link between food loss and micronutrient deficiency risks among women and children. Ultimately, this research supports the broader global agenda of sustainable food systems transformation, offering an interdisciplinary approach that integrates agriculture, nutrition, and public health for improved outcomes.

### Strengths of the study

This study offers a robust and contextually grounded investigation into post-harvest losses across the fruit and vegetable value chain in Ghana, with an emphasis on their nutritional implications. Employing a multistage sampling approach and integrating data from farmers, traders, and households will ensure representativeness and depth. The use of validated protocols for anthropometry, haemoglobin testing, and dietary assessments strengthens methodological rigour. Importantly, the study integrates context-specific dietary analysis by estimating nutrient intakes using the Ghanaian Food Composition Table, thereby ensuring cultural and dietary relevance and improving the accuracy of nutrient estimations. The inclusion of both anthropometric and biochemical assessments further strengthens the robustness and multidimensionality of the nutritional outcomes evaluated. Finally, the focus on women and children enhances the study’s public health relevance.

### Limitations of the study

This study has several limitations that should be considered. First, although the longitudinal design allows for tracking changes in fruit and vegetable waste and nutritional outcomes only at the household level over time, the follow-up period may not fully capture long-term effects. It is recommended that future studies extend the observation period to explore sustained impacts for all actors. Additionally, the assessment of fruit and vegetable waste relies on participants’ recall, which may introduce recall bias due to under- or overestimation. Finally, the study’s focus on a single district in Ghana may limit its generalizability to other regions with different agricultural practices, socioeconomic conditions, and seasonal availability of fruits and vegetables. Future research should include multiple districts to strengthen external validity and enable comparative analysis.
